## Abstract

**Background:**

Acute infectious diseases are major causes of short periods of days off from work, day care and school. These diseases are mainly caused by viruses and hands have a key role in their transmission. Thus, hypothetically, they can be controlled with means of intensified hand hygiene. In this study we aim to elucidate the effect of acute infectious diseases on the work contribution in common office work and study the influence of improved hand hygiene on possible reduction of infectious disease episodes and days off from work due to acute infectious diseases.

**Design:**

The voluntary participants have been recruited from six companies in the Helsinki region. The designated 21 study clusters were identified as operationally distinct working units each containing at least 50 people. The clusters were matched and randomized based on results of a pre-trial contagion risk survey. Improved hand hygiene is being executed with guided hand-washing with soap and water in one intervention arm and with alcohol based hand rubbing disinfectant in the other. Participants in both arms have received guidance on how to avoid infections and how to implement contagion stopping habits. A control arm is acting as before regarding hand hygiene. Data collection for evaluation of the efficacy of the interventions is based on self-reporting through weekly electronic reports. The questionnaire is enquiring about possible respiratory or gastrointestinal symptoms during the preceding week, and requests a daily report of presence of symptoms and working capacity. Etiology of the symptoms is not searched for individually, but contribution of different viruses is evaluated by sentinel surveillance, where occupational health clinics located in the premises of the participating companies collect specimens from employees visiting the clinic. Common causative agents of the diseases are being searched for using real-time PCR techniques. The duration of the intervention will be 16 months. Primary endpoints of the study are the number of reported infection episodes in a cluster within a time frame of 100 reporting weeks and the number of reported sick leave episodes in a cluster within a time frame of 100 reporting weeks.

**Trial Registration:**

ClinicalTrials.gov Identifier: NCT00821509

## Background

Respiratory tract infections (RTI) cause a large part of short periods of days off from work, day care and school. Gastrointestinal tract infections (GTI) are rarer in the working population, with sporadic norovirus or rotavirus outbreaks excluded. GTIs are, however, common in children, thus possibly leading to guardians' absence from work. Parents of children attending day care centers or in school are prone to RTIs and GTIs more often than other working population [1]. Often, because of the generally mild nature of the diseases, infected people come to work in spite of symptoms, and may therefore initiate transmission of infection among other workers. The chain of events from exposure to a pathogenic microbe to subsequent infection and generation of symptoms affecting working capacity is a very complicated one, and is influenced by many factors potentially causing variation, such as the multitude of causative agents, different natural immunities to the agents, and different individual histories of infections (Figure 1).

**Figure 1 F1:**
[figure not shown]
**Factors influencing viral infection induced periods of days off from work**. Steps in the process, from the point of view of an individual, are indicated in boldface by squares connected anticlockwise with each other by open arrows. Factors influencing translocation from one step to the following are shown in rounded squares and by black arrows to "regulation points" (crossed circle). Dashed open arrow represents contribution of viral load to the working team in case an infected individual remains at work or returns from home before the excretion period is over. Back-to-back triangles with **i **inside indicate the site of influence of improved hand hygiene at work and that of transmission-limiting behavior at work.

Acute RTIs are mainly caused by viruses. They are spread via excretions of the carrier with or without symptoms to respiratory tract, mouth or conjunctiva of a susceptible person. Viral GTIs are also spread via contaminated food or water. At least RTIs may be further spread via droplets or aerosols generated by coughing or sneezing. Hands have an essential role in the transmission; from direct contacts to contagion via contact surfaces, such as door knobs, taps in toilets, shared utility articles, table surfaces, to respiratory tract, mouth and eyes [2].

The effect of hand hygiene and advised behavior aimed at limiting the transmission of infections has been described in several research reports [3,4]. In recent meta-analyses, however, large part of the publications have been considered deficient in a way or an other, and due to differences in settings and variables affecting the final results comparison of the accepted studies has been problematic [5,6]. Based on earlier research and meta-analyses it seems, that improved hand hygiene may help in limiting the spread of infections in "semi-closed" environments with high infection pressure, especially in hospitals, but also in day care centers [7,8], schools [9] and military service [10]. In regular office work this has not been studied. Even though the annual epidemics of both RTI and GTI are familiar to everyone, there is little research based knowledge on the effect of acute infectious diseases on the work contribution in a defined working community, except in health care, children's day care and schools. One of the goals of this study is to elucidate the effect of acute infectious diseases on the work contribution in common office work.

In order to stop the spreading of difficult bacterial infections, alcohol based hand disinfectants are often used in hospitals instead of more traditional hand washing. In addition to the efficacy and the ease of use, the conversion to rub use has been justified e.g. with reduced total cost in a hospital setting [11]. Short treatment with alcohol does not, however, destroy all viruses, and there are reports suggesting that the spreading of the most common viral infections could be stopped with careful hand washing with soap and water at least equally well [6]. Hence, this study was designed to contain two intervention arms exploiting intensified hand-hygiene, one using water and soap, the other mainly an alcohol-based disinfectant. In this paper we describe the general design of the trial, try to justify the compromises we decided to make in the design in order to get the study going, and discuss obvious and potential weaknesses of the study some of which emerged only after launching the interventions.

## Methods

### Aim of the study and general description

This study is aiming at investigating the effect of improved hand hygiene on possible reduction of days off from work due to acute infectious diseases. The study is not designed to compare the two different hand cleaning techniques *per se *but includes two independent assessments of the combined efficacy of the advised transmission limiting behavior and intensified hand cleaning on the occurrence of RTI and GTI and consequent periods of days off from work in a common office work. Data collection for evaluation of the efficacy of the interventions is based on self-reporting through Monday-morning electronic reports using a simple standard format. The questionnaire is enquiring about possible symptoms of RTI or GTI during the preceding week, and requests a daily report (including weekends and other holidays) of presence of symptoms and working capacity. Etiology of the symptoms will not be searched for on individual basis in this study but a connection to concurrent RTI virus epidemiology is built by a sentinel surveillance, where occupational health clinics located in the premises of the participating companies send a standard number of weekly specimens collected from employees visiting the clinic. For possible GTI outbreaks a standard outbreak investigation principle will be followed, including 3-5 specimens from typical patients. Common causative agents of the diseases will be searched for using real-time PCR techniques. The duration of the intervention will be 16 months.

### Setting, identification of participating clusters and recruitment

Recruitment of participants was targeted to six companies in the Helsinki Region each including an occupational health clinic of their own. The participating companies include two leading retailers in Finland, two banks, a mining and metallurgical technology provider and a stainless steel producer. Only units involved in common office work were included. The premises of all companies were of the same kind including both open-plan offices and personal office rooms to some employees.

Participants were recruited in 21 operationally distinct volunteer groups, later referred to as study clusters, each including at least 50 persons. Operationally distinct means that members in a cluster had a likelihood of meeting other members of the same cluster during the daily working hours and shared certain physical spaces such as working room, toilets and/or refreshment/resting corners. Members of another cluster did not share these things but, in some cases, might be occasionally met, e.g., in a company restaurant.

Information about the purpose of the study and expected consequences of participating in it were given through different channels including posters and hand-outs, informative talks at staff meetings, and on company intranet web pages. Finally, everybody working in an identified cluster was sent an email requesting to answer a questionnaire about transmission risks (see below) and offering the possibility to participate in the study by weekly email reporting. Inclusion criteria were "Volunteers working in defined units". Exclusion criteria were "Persons with open wounds or chronic eczema in hands".

### Cluster matching and randomization

To minimize the effect of confounding factors the intervention clusters were matched and randomized prior to onset of the interventions. A questionnaire enquiring, among other things, about numbers and ages of children, their possible out-of-home day care, personal properties such as smoking, chronic diseases, and potential differences in contacts to other people during the daily work, was sent by email to all employees of the selected clusters (Additional file 1). An arbitrary virus transmission risk score was calculated for each cluster based on the results of these potential participant questionnaires [12]. First, the occurrence of each risk factor in a given cluster in relation to the frequency of the factor in the entire population interviewed was assessed. Next, these ratios were inter-connected to reveal an arbitrary transmission risk sum score for the cluster using the following formula:

Indicator variables:

x1 school aged or younger children

x2 at least one child under school age attending day care/pre-school classes/weekly club

x3 smoking (0 = if 1 or 2, otherwise > 1, see questionnaire in Appendix 1)

x4 medically diagnosed chronic heart condition, atherosclerosis, asthma or other respiratory disease

x5 mainly use of public transportation for commuting to work

x6 grown-up exposed to children with cold or vomiting/diarrhea disease at work in school, kindergarten, children's club, health care etc.

where s1-s6 denote corresponding unit-wise sums of each indicator, m1-m6 corresponding total sums over all clusters, i.e. border sums describing frequency of a given variable in the complete material and n, number of people in the cluster.

As can be judged from the above, living with pre-school children in day-care was considered the relatively strongest risk factor and the corresponding risk ratio multiplied by two in the formula. The clusters were then divided in groups of three most similar based on the calculated scores, and members of each triplet were randomized in one of the two intervention arms or in the control arm.

### Intervention arms and arm-specific guidance of hand hygiene and behavioral habits

A total of seven office units (247 reporting persons) belonged to intervention arm 1 (IR1), in which the intervention was based on hand-washing with soap and water. Further seven office units (199 reporting persons) belonged to intervention arm 2 (IR2), the alcohol disinfectant group. The remaining seven units (218 reporting persons) served as a control arm (IR0). The interventions were planned to continue more than 12 months, preferably one and a half year, in order to cover various season-dependent viral epidemics.

Improved hand hygiene was executed with guided hand-washing with soap and water in one intervention arm and with alcohol based hand rubbing disinfectant in the other. Participants in both arms also received identical guidance on and demonstration of how to avoid infections and how to implement contagion stopping habits. The guidance included instructions for proper coughing and sneezing, for avoiding hand shaking when possible, and frequent hand washing in office and at home. The guidance was given personally to all participants by a specifically trained research nurse and each participant also received written instructions for further reference. The participants in the intervention arms received free of charge containers of the relevant soap or disinfectant, respectively, to be used at home. Participants in the intervention arm 2 also received free of charge containers of disinfectant for personal use in the office. Participants in the control arm were advised to act as before regarding hand hygiene. Toilets and other hand washing spots in all participating clusters were equipped with the same soap, Erisan Nonsid Farmos, Finland, for hand washing. The alcohol containing hand rubbing disinfectant used was LV Käsihuuhde Berner, Finland.

The study was started in two steps following the progression of recruitment. The first batch included 12 units including 374 volunteers in total. The units were matched and randomized together to form four triplets. The second step included 9 units with 306 volunteers in total. These were matched and randomized together to form three triplets. The mean participation percentage in work units was 32.4%, which is reasonable given the large intra-class correlation [13] in the cluster expected in the study.

### Weekly reporting of exposure to infectious agent carriers and of day-by-day symptoms of infectious diseases and working capacity

The participants in all study arms are reporting weekly exposure to infectious diseases and own possible RTI or GTI symptoms and related days off work through internet. Every Monday the participants receive via email a link to an electronic questionnaire (Additional file 2). Design of the questionnaire, sending of the weekly calls for reporting, and replies containing database were executed with a commercially available provider of software services for feedback management and data collection Digium, Digium Enterprises, Espoo, Finland). The collected data is then further stored in an in-house database for monitoring and analyses.

### Drop-outs and post-onset enrollment of new participants

It was expected that some participants will give up weekly reporting of symptoms and days-off for various reasons or are, for operational purposes of the employer, translocated from their study cluster or leave the participating company. On the other hand, it was expected that before the end of the trial also new people are recruited by the employer to the study clusters. It was decided that since the follow-up week-based data will be primarily analyzed in a cluster specific way rather than targeting to individual participants, part time reports could be included in the data to be collected without problems. Likewise, individuals changing the study arms during the trial, first will provide data to the first arm, and after personal instructions relevant to the new arm, start to report to the other arm. Similarly, new recruits in the study clusters will be offered the possibility to participate in the trial and, after receiving training and instructions, will start reporting accordingly.

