### Study endpoints and outcome measures

#### Primary endpoints

a) the number of reported infection episodes in a cluster within a time frame of 100 reporting weeks

b) the number of reported sick leave episodes in a cluster within a time frame of 100 reporting weeks.

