## Discussion

### Potential limitations and emerged complications of the study

As mentioned in the introduction, the end-points of this trial, frequency of infectious disease episodes in office employees and that of the consequent periods of days off from work are influenced by a multitude of person-dependent and environmental factors. For some of the confounding factors attempts can be made to eliminate them or at least to minimize their effect while others cannot be regulated. Launching of the present intervention trial among the office staff of various commercial companies was coinciding with the international economical recession resulting in staff reorganization programs in some of the companies, which somewhat delayed and complicated our cluster definitions. A major challenge for the trial setup emerged after onset of the interventions, the influenza A/H1N1 pandemic that reached Finland in summer 2009 and prompted widely publicized improved hand hygiene campaigns at the national level, partly further detailed by the occupational health care units of the participating companies. Obviously, this influenced the behavior of the study participants in the control arm as well, even though it did not influence the participation percentage in the units. Some of the resulting compromises are discussed in the following.

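### Weeks reported after a change of arm, and weeks from employees recruited after allocation, enter the primary cluster rates; analysing by cluster does not remove carry-over or joiner selection

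*Protocol article*

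**What the plan says.** All references are to the protocol article.

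- **Randomisation.** Clusters were grouped in threes by risk score and "members of each triplet were randomized in one of the two intervention arms or in the control arm" (Cluster matching and randomization). This gives 21 clusters, seven per arm.
- **Primary endpoint.** The first is "the number of reported infection episodes in a cluster within a time frame of 100 reporting weeks"; the second has the same form for sick leave episodes. Every week reported from a cluster therefore enters its rate.
- **People who change arm.** The section on drop-outs and new participants says that "individuals changing the study arms during the trial, first will provide data to the first arm" and then, "after personal instructions relevant to the new arm, start to report to the other arm". It states no wash-out and no censoring.
- **People who arrive later.** The same section says "new recruits in the study clusters will be offered the possibility to participate in the trial", and that they report once trained.
- **Reason given.** Because the data are analysed mainly by cluster, "part time reports could be included in the data to be collected without problems".
- **Why people move.** Participants may be "for operational purposes of the employer, translocated from their study cluster or leave the participating company". The Discussion adds that the recession was "resulting in staff reorganization programs in some of the companies".
- **Planned checks.** Evaluation of matching and comparability between the arms repeats the risk questionnaire at trial end, compares drop-outs and recruits at six-month intervals, and compares hygiene-survey results.

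**The concern.** This is a decided rule with a stated reason, not a detail left to an analysis plan, and the reason does not hold. There are two separate mechanisms.

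**Carry-over.** The intervention is taught behaviour: personal guidance and demonstration, written instructions, hand washing at home as well as in the office, and free supplies for home. None of this is undone when a person moves to a control unit, yet the later weeks count as control weeks. The article accepts this mechanism elsewhere. In the section on the H1N1 pandemic it expects hand hygiene taken up in the control arm to dilute the difference, and it splits the analysis into two parts for that reason.

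**Joiner selection.** The first volunteers were invited in the same mailing as the risk questionnaire, whose results were needed for matching, so they came forward before allocation. Later recruits decide in a unit whose arm can be seen from its supplies and from the nurse's monthly visits. Mean participation was 32.4%, so about two in three people did not take part, which leaves room for the arm to influence who does. The outcome is self-reported, so the kind of person who volunteers matters.

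At stake is an effect that the article expects to lie nearer the lower end of 10% to 50%.

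**Working it through.** The article gives no sample size, power or turnover figure, so there is nothing to reproduce. The calculations below are illustrations on assumed inputs.

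**1. Carry-over.** Let *e* be the true relative reduction and *m* the share of control weeks supplied by former intervention participants who keep the full effect (both assumed). The control rate falls by the factor 1 − *m·e*, so the observed reduction is 1 − (1 − *e*)/(1 − *m·e*).

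- *e* = 15%, *m* = 5%: 1 − 0.85/0.9925 = 14.4%
- *e* = 15%, *m* = 20%: 1 − 0.85/0.97 = 12.4%
- *e* = 10%, *m* = 5%: 1 − 0.90/0.995 = 9.5%
- *e* = 10%, *m* = 20%: 1 − 0.90/0.98 = 8.2%

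If only half the effect is retained, the *e* = 10%, *m* = 20% case gives 1 − 0.90/0.99 = 9.1%.

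**2. How large could *m* be?** Two assumptions give very different answers. The arms have 247 + 199 = 446 intervention reporters and 218 control reporters.

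- *Half of the intervention movers go to control.* Suppose 10% of each arm leaves mid-trial. Movers supply 446 × 0.10 × 0.5 × 0.5 = 11.2 person-trials. Remaining controls supply 218 × 0.95 = 207.1. The share is 11.2/218.3 = 5.1%.
- *Movers land at random among about 10,000 staff.* The 374 + 306 = 680 volunteers at 32.4% participation imply roughly 2,100 staff in study clusters. About 700 of them are in control clusters, or 7% of all staff. To supply 5% of control weeks from mid-trial moves takes about 2 × 0.05 × 218 = 22 people arriving in control. That needs about 22/0.07 = 314 movers out of 446. For 20%, about 87 arrivals would need over 1,200 movers, more than exist.

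Reorganisation of whole teams could break the random-landing assumption. Even so, 20% is better read as an outer bound than as a plausible value.

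**3. Joiner selection.** Let *q* be the joiners' share of the intervention arm's weeks and *s* their underlying rate relative to the first volunteers (both assumed), with joiners in that arm only. With no true effect, the spurious relative difference is *q* × |1 − *s*|.

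- *q* = 20%, *s* = 0.85 or 1.15: 0.20 × 0.15 = 3%
- *q* = 20%, *s* = 0.8 or 1.2: 0.20 × 0.20 = 4%
- *q* = 30%, *s* = 0.7 or 1.3: 0.30 × 0.30 = 9%

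With a true 10% reduction and *q* = 20%, the observed reduction is 1 − 0.90 × 0.96 = 13.6% at *s* = 0.8, and 1 − 0.90 × 1.04 = 6.4% at *s* = 1.2. If similar joiners entered all arms in similar numbers, the difference would largely cancel.

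**4. Scale within a cluster.** Control clusters average 218/7 = 31 reporters, so about six people make up 20% of one cluster.

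**The case against.** The strongest reply is that a reader might infer more than the text supports.

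- **Randomisation is lost, or the analysis is as-treated.** Neither follows. Clusters were randomised, and nothing moves a cluster to another arm. Counting each week where the person then works is a recognised open-cohort design and suits a question about contagion in shared workspaces. An as-treated analysis would reclassify people by the hygiene they actually practise. What is lost is only a set of individuals fixed before allocation.
- **People are counted twice.** They are not. Each week counts once.
- **All moves dilute the effect.** Only moves from an intervention arm to control do. Moves from control bring no intervention habits with them, and moves between the two intervention arms hardly affect either comparison with control.
- **Movers choose their arm.** The article attributes transfers to the employer's needs, which weakens selection by arm among movers. It does not affect carry-over.
- **Anyone may join late.** The text refers to new employees. It does not describe existing non-volunteers joining after learning their arm.

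These points stand and limit the finding. The planned checks help less. The repeated risk questionnaire does address whether changed membership altered comparability, but all three checks describe imbalance and none leads to a change in the analysis.

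It is also fair to say that a closed cohort as the primary analysis would be a debatable trade: it shrinks over time, in a trial already split into parts of 25 and 43 weeks. Stopping the count at transfer is itself an exclusion after randomisation. Employer-driven moves make it less likely to bias the comparison, and a version that keeps the later weeks can test it.

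**Conclusion.** The concern holds in a limited form. The comparison is still randomised at cluster level, but the claim that these reports can be included without difficulty is not justified by analysing by cluster.

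Carry-over biases towards no effect and is probably small: less than 3 percentage points off a true 15% reduction even at the outer bound, and about half a point at 5% of control weeks. Joiner selection has no fixed direction. It is 3% to 4% on moderate assumptions and could approach the expected effect only on more extreme ones.

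All of these sizes rest on assumed turnover, retention and rate differences, because the article gives no count of movers or joiners. The case for acting is that the expected effect is near the low end of 10% to 50% and the protection is cheap.

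**What to change.** 1. In the primary cluster rates, stop counting a participant's weeks from the date of transfer to a cluster in a different arm.
2. Prespecify a sensitivity analysis limited to volunteers enrolled before their triplet was randomised, analysed by cluster and arm of enrolment. Add one version that keeps movers' later weeks in the arm of enrolment.
3. Report the numbers of movers and joiners, and the weeks they supply, by arm and by direction of move.
4. Delete the statement that such reports can be included without problems. Say instead that the design is an open cohort, and name the two sources of bias.

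The open-cohort inclusion of new employees can stay in the primary analysis, with item 2 showing whether it matters.

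**Cost.** Slightly fewer reporting weeks in the primary rates and a little more analysis work. No new data are needed, since reports are dated and email address and working unit are held. Data collection runs to May 2010 and the primary analysis starts in June 2010, so on that timeline the rule can be fixed before the final data are analysed. The first part, to the end of July 2009, should follow the same rule.
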